#### Exploratory outcomes

2.11.3

Sensitivity, specificity, and positive predictive value of the sIgE/tIgE ratio and basophil activation test (BAT) in predicting positive OFC outcomes for each form of hen's egg will be also assessed.

### Concomitant care

2.12

If a participant is suspected of having a food allergy other than HEA, appropriate diagnostic and management procedures will be implemented. However, to preserve the internal validity of the study, any concurrent interventions that could potentially confound study outcomes, such as immunotherapy, will be contraindicated during the study period.

Parents will be instructed to promptly contact the study physician if any health concerns arise.

### Study discontinuation criteria

2.13

Participant withdrawal from the study may occur under the following circumstances: voluntary withdrawal of consent by one or both parents/legal guardians, any perceived risk to the child's health, non-adherence to the study protocol, loss of contact with the participant, or the formal conclusion of the study.

In the event of premature withdrawal, the investigator will ensure that all evaluable endpoints are documented in the Clinical Research Form (CRF), unless the parents/legal guardians explicitly refuse further participation. If the discontinuation of the intervention is due to a confirmed and/or potential adverse event, the child will continue to be monitored, with all relevant observations recorded in both the medical records and the CRF.

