#### Duration of each ladder step and reintroduction of HEPs at home

2.5.2

The literature lacks a standardized egg ladder protocol, including the time intervals between its consecutive stages. Scientific societies suggest intervals ranging from 1 to 9 months (12–16). In the Canadian egg ladder protocol, a 1–3 month interval between stages is recommended (13). In this study, based on our own clinical experience, we hypothesized that a 6-week interval would be sufficient to assess the acquisition of tolerance to each subsequent stage of the egg ladder.

Following a negative OFC result and careful 24-h home observation, parents will be instructed to regularly reintroduce hen's egg proteins at home. This study follows the BSACI guidelines (15), which recommended the administration of hen's egg proteins three times per week. Over a six-week period, caregivers will introduce hen's egg proteins in the same quantity and form that did not elicit an allergic reaction during the preceding OFC.

Participants progressing to advanced EL stages will incorporate into their diet the dose of hen's egg proteins tolerated during the previous OFC, along with one to two additional portions of hen's egg proteins products from lower EL steps. The total intake should not exceed three hen's egg proteins-containing products per day. To ensure safety, home consumption of higher-step EL products is not permitted until tolerance has been confirmed through a hospital-based OFC.

Tested food products and their amount were developed according to the BSACI (15) and PRACTALL guidelines (7) and RCT by de Vlieger et al. (12) (Table 2).

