#### Primary outcome

2.11.1

The primary outcome is the percentage of children who acquire tolerance to soft-boiled hen's egg (almost raw hen's egg proteins), as determined by a negative OFC at the final step of the EL. Soft-boiled egg will be administered at the end of the observation period (18 or 24 weeks, depending on the assigned study arm).

The challenge dose will consist of 0.5–1 egg for children aged 1–3 years and 1 egg for those aged 4–5 years, corresponding to a maximum total of 6 g of hen's egg proteins. The outcome will be reported as a difference between two study arms.

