### Statistical analysis

2.19

Descriptive statistics will be used to summarize baseline characteristics. For continuous variables, comparisons between groups will be made using the Student's *t*-test, Mann–Whitney *U*-test or Wilcoxon signed rank test, depending on whether or not the variables are normally distributed. The appropriate statistical test will be employed to compare percentages, either the χ^2^ test or Fisher's exact test.

For continuous outcomes, the differences in means or medians (depending on the distribution of data), and for dichotomous outcomes, the relative risk (RR) and number needed to treat (NNT), all accompanied by a 95% CI, will be calculated. The difference between study groups will be considered statistically significant if the *p*-value is less than 0.05, if the 95% CI for RR does not include 1.0, or if the 95% CI for mean difference does not include 0. All statistical tests will be two-tailed and performed at the 5% level of significance.

An intention-to-treat (ITT) analysis including all randomised participants, regardless of protocol adherence or withdrawal, will be applied. A per-protocol analysis that includes all participants who finish the study according to the protocol will also be performed.

The number of missing data with reasons will be reported for each study arm, and compared qualitatively between groups, if feasible. Multiple imputation methods for missing data will be applied to address missing data, as recommended (34).

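### Undefined non-adherence is a ground for leaving the study itself, which creates avoidable missing primary outcomes and conflicts with the stated intention-to-treat analysis

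*Protocol article*

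**What the plan says.** All references are to the protocol article.

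- **2.13 Study discontinuation criteria.** Withdrawal from the study may occur after withdrawn consent, a perceived health risk, "non-adherence to the study protocol, loss of contact with the participant, or the formal conclusion of the study". Non-adherence has no threshold, and nobody is named as deciding. For a child who leaves early, the section states: "the investigator will ensure that all evaluable endpoints are documented in the Clinical Research Form (CRF), unless the parents/legal guardians explicitly refuse further participation". The promise to go on following the child is narrower: "If the discontinuation of the intervention is due to a confirmed and/or potential adverse event, the child will continue to be monitored".
- **2.11.1 Primary outcome.** Tolerance is judged "as determined by a negative OFC at the final step of the EL". That step is reached through successive hospital challenges; under 2.5.2, "home consumption of higher-step EL products is not permitted until tolerance has been confirmed through a hospital-based OFC".
- **2.19 Statistical analysis.** "An intention-to-treat (ITT) analysis including all randomised participants, regardless of protocol adherence or withdrawal, will be applied". A per-protocol analysis is planned as well. For gaps in the data, "Multiple imputation methods for missing data will be applied to address missing data".
- **2.6.1.** If the allergen is not given for more than a week, the next challenge is delayed in proportion, so the child is kept.
- **2.11.2.** Full adherence is a secondary outcome, compared between arms.
- **Table 2 and 2.17.** The 4-step ladder has three six-week home intervals (18 weeks) and the 5-step ladder has four (24 weeks). Everyone, including outcome assessors, knows the allocation.

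**The concern.** The analysis section treats adherence as irrelevant to who is analysed, while the discontinuation section lets a child leave the study because of it. A child who leaves part-way up a sequential ladder has no planned route to the final challenge, so the primary outcome is missing and has to be imputed. That loss is avoidable, because it follows from a rule in the protocol and not from a family's refusal or disappearance.

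The loss could also differ by arm. The 5-step ladder has one more interval in which to fall behind, allocation is open, and the Discussion itself notes that some parents may prefer the other ladder, for example because the shorter one may mean fewer hospital visits. The same child with a long break could be kept under 2.6.1 or withdrawn under 2.13. At stake are the primary comparison and the adherence outcome, which is cut short for the very children it is meant to describe.

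**Working it through.** **Passages side by side.** Three places keep a non-adherent child and measure the behaviour: 2.6.1 extends the interval, 2.11.2 counts adherence, and 2.19 analyses everyone randomised. One place, 2.13, lets the child leave. Its sentence on evaluable endpoints does not close the gap, since a final OFC that was never performed is not an evaluable endpoint.

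**The plan's own figure.** Section 2.9 wants 42 completers per group with 10% dropout: 42 / (1 − 0.10) = 46.7, rounded up to 47 per group, 94 in total. This reproduces. Expected dropout is 94 × 0.10 = 9.4 children from all causes.

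**Missingness from unequal length alone.** Assume the same withdrawal risk q in every home interval of both arms. The proportion withdrawn is then w4 = 1 − (1 − q)³ in the 4-step arm and w5 = 1 − (1 − q)⁴ in the 5-step arm. Setting (w4 + w5) / 2 = 0.10 gives q = 2.97%, hence w4 = 8.64% and w5 = 11.36%. Per 47 children that is 4.1 versus 5.3, a difference of about one child.

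**Effect on the primary difference.** Let p be tolerance among continuers, equal in both arms, and suppose the imputation reproduces p. The imputed difference is 0. If withdrawn children were instead counted as not tolerant, the difference would be p(1 − w4) − p(1 − w5) = p(w5 − w4). The value p = 69% is the pooled figure in the Introduction; all withdrawal rates are assumptions.

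| Assumption | w4 v w5 | Shift at p = 69% |
|---|---|---|
| q = 2% | 5.9% v 7.8% | 1.3 points |
| q = 2.97% (10% overall) | 8.6% v 11.4% | 0.69 × 2.71 = 1.9 points |
| q = 5% | 14.3% v 18.5% | 3.0 points |
| Unequal, chosen | 5% v 10% | 3.5 points |
| Unequal, chosen | 5% v 15% | 6.9 points |
| Equal proportions | any | 0 |

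Across the 50% to 85% interval that the Introduction gives around the 69%, the second row runs from 0.50 × 2.71 = 1.4 to 0.85 × 2.71 = 2.3 points.

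**If withdrawn children have some tolerance t.** The shift becomes (p − t)(w5 − w4). For t between 30% and 0%, 4 versus 5 withdrawn of 47 gives 0.39 × 1/47 = 0.8 to 0.69 × 1/47 = 1.5 points. With 2 versus 8 withdrawn it is 0.39 × 6/47 = 5.0 to 0.69 × 6/47 = 8.8 points. It is 0 if t = p.

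**Extreme bounds.** With 4 versus 5 missing and 69% tolerance observed (30 of 43 and 29 of 42), the risk difference can lie anywhere from (30 − 34)/47 = −8.5 to (34 − 29)/47 = +10.6 points. The cited egg trial found 80% versus 69%, a difference of 11 points.

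**The case against.** Several points on the other side are sound.

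- A reader might infer that investigators who know the arm will decide whom to remove. Section 2.13 says only that withdrawal may occur and names no decision-maker.
- A reader might infer that intention-to-treat is broken. It is formally kept: all randomised children stay in the analysis set and missing outcomes are imputed. What weakens is the share of that analysis that rests on observed outcomes.
- A reader might infer that a withdrawn child simply receives the continuers' success rate. No imputation model is stated, and that detail may properly sit in a statistical analysis plan that is not shown. A model could use arm, earlier challenge results, specific IgE, basophil activation and diary data. The zero imputed difference above is therefore an assumption.
- A split such as 5% versus 15% has no source in the protocol. It averages 10% and would use up the whole dropout allowance.
- Ordinary lapses are catered for by extended intervals and, under 2.14, by another form of the food when feeding is difficult. Frequent removal is therefore less plausible.
- Counting every non-adherent child as not tolerant in the primary analysis would change the question to a composite of tolerance and adherence. A child who missed portions may well be tolerant.
- Some non-adherence, such as giving higher-step foods at home early, breaches safety rules.

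These points limit the size of the problem and the remedy. They do not remove the contradiction between 2.13 and the other sections. A later analysis plan also cannot recover a challenge that was not done. Children with a positive OFC, who leave under 2.5.3, are a separate matter because their failure is observed.

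**Conclusion.** The point holds in a limited form. The protocol allows exit from the study for undefined non-adherence, does not secure the final OFC or other follow-up for these children, and thereby contradicts its own analysis section, its handling of missed doses and its adherence outcome. The result is avoidable missing primary outcomes that may differ by arm.

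The likely bias is small: about 1.9 points at most under equal risk per interval, 10% overall dropout made up entirely of non-adherence, and 69% tolerance among continuers. Shifts of roughly 5 to 9 points need clearly unequal withdrawal, which is possible in an open-label trial but is not something the documents predict. They do not support a claim that a large bias is expected or that the trial is no longer analysed by intention to treat. The change is worth making because the contradiction is plain and the correction cheap.

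**What to change.** In 2.13, delete non-adherence as a ground for leaving the study and separate discontinuing the ladder from leaving the study. State that all outcomes continue to be collected for such children, including the final OFC where the study's own safety rules allow it, unless consent is withdrawn or contact is lost. In 2.19, handle adherence in the per-protocol analysis, and add a sensitivity analysis that counts children who did not reach the final OFC because of non-adherence as not tolerant. Reconcile 2.6.1, 2.11.2, 2.13 and 2.19 accordingly. How the ladder itself is managed for these children is left to the investigators.

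The cost is a few sentences, slightly more follow-up work and one extra analysis.

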### Study modifications

2.14

In the event of adverse events occurring during an oral food challenge (OFC), the procedure will be immediately discontinued, and appropriate medical management will be initiated based on the child's clinical presentation, in accordance with the department's standard protocols. The interval between subsequent steps of the egg ladder will be determined on an individual basis.

If an adverse reaction occurs following the consumption of a tested food item at home, the child will be examined by the attending physician to determine the appropriate course of action.

In case of substantial feeding difficulties, different form of tested form may be proposed to a child. However, the same amount of hen's egg proteins per serving and temperature and heating settings must be maintained (e.g., crepes instead of pancakes; hardly cooked scrambled eggs instead of hard-boiled egg).

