#### Supervised oral food challenge

2.5.1

Oral food challenges at each step of the egg ladder will be conducted under hospital conditions by a research physician. Data on the hen's egg protein content in the study products (per portion and per 100 g) are presented in Table 2.

Prior to each OFC, parents will receive detailed recipes for home preparation of the products, as well as information on medications that must be discontinued before the OFC (Supplementary Material 1). OFC will be performed after a minimum four-hour fast. For younger children, a light, low-fat snack (equivalent to 0.5 of a standard portion) may be allowed two hours prior to the scheduled challenge.

In accordance with PRACTALL consensus (7) the OFC will be conducted using a four-dose challenge protocol (1/16–1/8–1/4 – and the remaining amount of a muffin), with 30-minute intervals between each administered portion of the tested product. Following the final dose, the patient will be monitored in an inpatient setting for two hours. If no adverse reaction occurs, the child may be discharged and should be closely observed at home by a parent for an additional 24 h to rule out any delayed allergic reactions.

While the double-blind, placebo-controlled food challenge is considered the gold standard for the diagnosis of HEA (15), we will conduct open-label OFCs to enhance feasibility and encourage parental cooperation. To reduce bias, we will use the predetermined stopping criteria based on objective signs.

Despite providing standardized recipes and instructing parents to strictly follow the instructions, there is still a possibility of inaccurate food preparation (e.g., baking nine muffins instead of eight). Therefore, prior to each OFC, a researcher will weigh the test product (e.g., muffin or other food item) to precisely estimate the actual amount of hen's egg proteins consumed by the child. Both the tested portion and the total amount of the prepared egg-containing food will be weighed and recorded

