### Follow-up

2.8

Patients will be followed up by the research team to assess their ongoing tolerance and continued inclusion of egg in their diet at 6 weeks after completing the EL.

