#### Secondary outcomes

2.11.2

All secondary outcomes will be reported as a difference between two study arms.
The percentage of children with a negative OFC at each step of the EL protocol upon completion of the study's observation period (18 weeks and 24 weeks, depending on the study arm), calculated as the proportion of children tolerating the full planned dose for each step.The proportion of children who experience anaphylaxis during the observation period (18 or 24 weeks, depending on study arm), defined as reactions with severity grades 3–5 according to the updated 2023 WAO clinical criteria for anaphylaxis (27).The proportion of children with anaphylaxis (grades 3–5, per 2023 WAO criteria) who required epinephrine administration, categorized by:
○one or two doses of intramuscular epinephrine with a good clinical response (less severe reaction, grade 3),○more than 2 doses of intramuscular epinephrine,○lack of significant clinical improvement after two doses (severe reactions, grades 4–5),○measured during the observation period (18 or 24 weeks, depending on the study arm).The proportion of children who experienced systemic allergic reactions (SAR) of grades 1, 2, and 3 according to the 2023 WAO grading system, with specific reference to gastrointestinal symptoms:

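### A child withdrawn because the study food caused an allergic reaction at home can, as the plan is written, be multiply imputed as tolerant

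*Protocol article*

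**What the plan says.** All references are to the protocol article.

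- **Primary outcome (2.11.1).** Tolerance to soft-boiled egg is established "as determined by a negative OFC at the final step of the EL". The step-level secondary outcome (2.11.2) also rests on the OFC: it is "calculated as the proportion of children tolerating the full planned dose for each step".
- **Reaction in hospital (2.5.3).** Set criteria make the OFC positive. Progression and study participation then end, so the failure is observed.
- **Reaction at home (2.14).** "If an adverse reaction occurs following the consumption of a tested food item at home, the child will be examined by the attending physician", who decides on the course of action. No outcome value is attached.
- **Withdrawal (2.13).** Concern for the child's health is one permitted ground. Evaluable endpoints are to be documented, and a child who stops for an adverse event stays under observation. Again no outcome value is assigned.
- **Analysis (2.19).** The ITT analysis takes in every randomised child, including those who withdraw. "Multiple imputation methods for missing data will be applied to address missing data", with no distinction by reason for stopping.
- **First day after an OFC (2.5.1, 2.5.2).** The child is to be "closely observed at home by a parent for an additional 24 h to rule out any delayed allergic reactions". The next section lists this separately from the result: "Following a negative OFC result and careful 24-h home observation", home introduction begins.
- **After the ladder (2.8).** A contact is planned "to assess their ongoing tolerance and continued inclusion of egg in their diet at 6 weeks after completing the EL". It is not among the listed outcomes.

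**The concern.** Multiple imputation in its usual form predicts a missing result from children who resemble the missing child and whose result was seen. That is reasonable for a family that moves away. It is not reasonable when the child has no final OFC because the study food caused an allergic reaction. There the reason for the gap is itself strong evidence of non-tolerance, and the children who supply the imputed values are largely those who could continue.

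Two things are at stake. Both arms' tolerance rates may be too high, since some failures of the strategy are turned into successes. The comparison between arms may also be biased if reaction-driven stops are more common in one arm. That is plausible, because the arms differ both in starting dose and in the number of home intervals before the final OFC (three in the 4-step ladder, four in the 5-step ladder).

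**Working it through.** **1. Tracing one child through the text.** A child passes an early step in hospital, reacts to the same food at home, is examined under 2.14 and is withdrawn under 2.13. There is no positive OFC, so 2.5.3 does not record a failure. There is no final OFC, so 2.11.1 has no result to read. Under 2.19 the child remains in the ITT set and missing data are imputed. No sentence takes this child out of the imputation.

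**2. The plan's own figure.** Section 2.9 gives 42 completers per arm and 10% dropout: 42 / 0.9 = 46.7, rounded up to 47 per arm, 94 in total. This reproduces. The plan gives no figure for home reactions, so the size below is an illustration.

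**3. Inputs.**
- Home intervals before the final OFC: 3 (4-EL, 18 weeks) and 4 (5-EL, 24 weeks), from 2.1 and Table 2.
- Tolerance among children not stopped: p = 0.69, the pooled rate for raw egg from the 2024 meta-analysis cited in the Introduction (95% CI 0.5 to 0.85), applied to both arms.
- Risk per interval of a reaction that ends the ladder: h = 1% to 10%, **assumed**, equal in every interval and both arms.
- Imputation that makes no use of the reaction, so that it returns p for stopped children: **assumed**.

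**4. Formulas.** Share stopped with k intervals: 1 − (1 − h)^k. Rate if stopped children are imputed: p. Rate if they count as not tolerant: p(1 − h)^k. Shift in the arm difference: p[(1 − h)^3 − (1 − h)^4].

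Worked for h = 5%: 1 − 0.95^3 = 0.143 and 1 − 0.95^4 = 0.185, about 6.7 and 8.7 children of 47. The rates become 0.69 × 0.857 = 59.2% and 0.69 × 0.815 = 56.2%, against 69% in both arms when imputed.

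| h | Stopped 4-EL | Stopped 5-EL | Not tolerant rule, 4-EL | Not tolerant rule, 5-EL | Shift (points) |
|---|---|---|---|---|---|
| 1% | 3.0% | 3.9% | 67.0% | 66.3% | 0.7 |
| 2% | 5.9% | 7.8% | 64.9% | 63.6% | 1.3 |
| 5% | 14.3% | 18.5% | 59.2% | 56.2% | 3.0 |
| 10% | 27.1% | 34.4% | 50.3% | 45.3% | 5.0 |

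The rate within an arm is inflated by 69% minus the table entry: 2.0 to 18.7 points in 4-EL and 2.7 to 23.7 points in 5-EL. Over the confidence interval for p, the shift at h = 5% runs from 0.50 × 0.0429 = 2.1 to 0.85 × 0.0429 = 3.6 points.

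**5. Direction.** With equal risk per interval, imputation flatters 5-EL only because it has one more interval. That interval uses the lowest-dose muffin, so its risk may be lower than the others. If it were zero, the shift would be zero. If instead h were 5% in 4-EL and 2% in 5-EL, the shift would be 0.69 × (0.143 − 0.078) = 4.5 points in favour of 4-EL.

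**6. Limits.** The formula keeps every child at risk in every interval, although some leave earlier after a positive OFC, so it overstates the share stopped for a given h. At h = 5% and above, the stopped share alone exceeds the 10% total dropout that the protocol expects.

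**The case against.** The best case on the other side has four parts.

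- **Imputation is only one path.** The physician may let the child go on, and the next OFC then decides. Withdrawal is optional, and nothing expressly codes a withdrawn child as missing. A reader could equally hold that a child without a negative final OFC simply fails the definition in 2.11.1. *This stands against any claim that such a child will be imputed.* It does not remove the problem: the text allows both readings, and they give different primary results.
- **This is detail for an analysis plan.** Imputation models usually are. But the article itself states an imputation rule without exception alongside the ITT set, and it defines the primary outcome. How reaction-driven stops count belongs to that definition.
- **An OFC-only endpoint is safer in an open-label trial.** Home reactions are first reported by parents who know the allocation, whereas the OFC has predetermined objective criteria. *This stands as a defence of the final endpoint.* It is also a real cost of the fix, which is why the fix asks for confirmation by the physician and a sensitivity analysis.
- **The effect is small and assumed.** A shift of 0.7 to 5.0 points compares with a standard error for the arm difference of √(2 × 0.69 × 0.31 / 47) = 9.5 points. That is fair for precision, but the error is systematic, and the inflation within each arm is larger than the shift.

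Home reactions are not lost as safety data: the diary (2.7) and harms reporting (2.15) capture them. That does not settle how they enter the efficacy outcome.

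**Conclusion.** The point holds in a limited form. A child withdrawn because of an allergic reaction to the study food at home has no OFC result that records the failure, and the stated rules allow that child to be imputed as tolerant. The 0.7 to 5.0 point shift is an illustration that rests on the assumed rates and equal risk across intervals, not an estimate. It merits a change of wording before the analysis is fixed.

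A reader might infer more than the documents support:

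- *That home reactions never count against tolerance.* A reaction in the 24-hour observation may be meant as part of the OFC. Sections 2.5.1 and 2.5.2 leave this open, and the positive-OFC criteria are in a supplement that is not shown.
- *That the error is larger in the 5-step arm.* This follows only if the risk is similar in every interval, which nothing in the documents establishes.
- *That a child who reacts to soft-boiled egg at home after passing the final OFC is wrongly counted.* That child meets the stated endpoint, and judging tolerance by the supervised challenge is a legitimate choice.

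**What to change.** In 2.11.1 and 2.19, state that in the ITT analysis a child who permanently stops the ladder because of an allergic reaction to the study food, confirmed at the physician examination already planned in 2.14, counts as not tolerant. Limit multiple imputation to stops unrelated to reactions. Record the reason for stopping in the CRF. Report the analysis that imputes all such children as a sensitivity analysis.

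Reconcile 2.5.1 with 2.5.2 on whether a reaction during the 24-hour home observation makes the OFC positive. Reporting tolerance at the 6-week follow-up (2.8) as a supportive outcome is optional.

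The cost is protocol and analysis-plan wording plus one CRF field, with no new visits. Reported tolerance rates become slightly less favourable, and some unblinded judgement enters the outcome; the sensitivity analysis shows how much depends on it. The change concerns classification in the analysis only, not how a reaction is managed.
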